**Rational**

Iron is an essential element that is crucial to all major metabolic pathways. Among others, it plays a central role in the proteins that transport oxygen in the blood and muscles, i.e. haemoglobin and myoglobin, respectively. The metabolism of iron is highly regulated with efficient recycling of iron but no active excretion of iron. Homeostasis is typically maintained at the level of intestinal absorption; however, iron deficiency may arise from blood loss, impaired uptake, dietary deficiency and developmental demands such as pregnancy. Iron deficiency is one of the most common nutrient deficiencies affecting an estimated two billion people worldwide (WHO health report 2002). If untreated, iron deficiency may lead to iron deficiency anaemia, whereas anaemia affects almost 25% of the world's population. Iron deficiency anaemia has been linked to impaired physical and mental development, fatigue, weakened immunity, poor work performance and a decreased quality of life.

Treatment ultimately involves identifying the underlying cause of the iron deficiency and replenishing the iron stores. Currently, oral supplementation is the first-line treatment though a significant number of patients do not tolerate or do not respond to oral iron therapy. In some studies, as many as 40% of patients reported side effects secondary to oral iron intake. Reported side effects usually occur within an hour after ingestion and include nausea, epigastric pain, vomiting, diarrhoea or constipation. Further limitations of oral iron treatment are impaired absorption, prolonged iron store repletion times and, particularly with concomitant erythropoiesis-stimulating agent (ESA) treatment, increased iron demands that cannot be matched by oral iron supplementation. Accordingly, a significant number of patients discontinue oral therapy despite substantial iron deficiency and require IV iron as an alternative approach.

Intravenous iron therapy is suitable in the following clinical situations:

a) intolerance to oral iron preparations; b) severe iron deficiency where a rapid therapeutic effect is needed; c) functional iron deficiency where the iron demand for haemoglobin synthesis exceeds the amount that can be mobilised from filled iron stores, e.g. in anaemia of inflammation or while using ESAs d) iron deficiency, where oral iron therapy is insufficient because of chronic blood loss; e) malabsorption of iron due to intestinal disorders; f) poor compliance to oral iron treatment: g) risk of drug-drug interactions between oral iron and concomitant medication.

[figure not shown]

[name]; PhD; FASN.  
Professor of Medicine University of Buenos Aires  
Chief of Nephrology.  
Hospital Alemán, [name]  
Buenos Aires (1118)- Argentina  
[contact]  
[contact]  
Mobile [contact]  
E-mail: [contact]

Until recently, the most commonly used IV iron preparations comprised iron Dextran, iron gluconate, and iron sucrose. Although effective in replenishing iron stores, each of these formulations has distinct limitations. Iron Dextran is associated with reactivity to anti-Dextran antibodies that can induce hypersensitivity reactions and anaphylactic shock. On the other hand, less robust iron complexes such as iron gluconate and to lower extent iron sucrose release larger amounts of iron into the plasma. This can cause oxidative stress and loss of administered iron via renal excretion rather than incorporation into iron-binding proteins for utilisation in erythropoiesis. In an attempt to overcome these limitations, ferric Carboxymaltose has been developed as a novel IV iron repletion therapy.

Ferric Carboxymaltose represents a new generation of parenteral iron preparations that is currently approved in 17 EU countries (Austria, Czech Republic, Denmark, Estonia, Finland, Germany, Greece, Ireland, Latvia, Lithuania, The Netherlands, Poland, Portugal, Slovak Republic, Spain, Sweden and UK) as well as in Liechtenstein and Switzerland. During development the aim was to create a product that addresses the limitations of currently available IV iron products. In particular, the goal was to develop a formulation with the following properties:

1-dextran-free and thus not reactive with anti-dextran antibodies; 2-safe to be administered in a high dose; 3- administered over a shorter time than current products; 4- heat sterilisable; 5- pH-neutral and nearly isotonic.

Ferric Carboxymaltose is a Dextran-free iron complex consisting of a polynuclear iron (III) oxo-hydroxide core stabilised with a carbohydrate shell. The core of ferric Carboxymaltose resembles that of ferritin, the main intracellular iron storage protein. Ferric Carboxymaltose is taken up in the reticuloendothelial system of the liver, spleen, and bone marrow. The complex is degraded and the iron is made available for utilisation, i.e. incorporation in haemoglobin, or storage, i.e. incorporation in ferritin. As only very small amounts of unbound, labile iron are released into the circulation, the toxic effects of labile iron are avoided.

Ferric Carboxymaltose is a more stable complex than iron gluconate and iron sucrose. Consequently, it allows for administration of high single doses of iron. Despite the improved stability of iron sucrose compared to iron gluconate, both have to be administered at lower dosages than ferric Carboxymaltose, requiring more interventions for the patient and doctor.

Because of the efficient delivery of usable iron directly to the bone marrow, IV Ferric Carboxymaltose can play a vital role in treating anaemia of patient with CKD when used in combination with ESAs.

[figure not shown]

[name]; PhD; FASN.  
Professor of Medicine University of Buenos Aires  
Chief of Nephrology.  
Hospital Alemán, [name]  
Buenos Aires (1118)- Argentina  
[contact]  
[contact]  
Mobile [contact]  
E-mail: [contact]

In agreement with this statement, several randomised studies in oncology patients have shown that ESAs were more effective when used with IV iron than with oral iron formulations alone. Furthermore, IV reduces the dose of ESAs required to achieve the target haemoglobin level. Once again, in patients with cancer-related anaemia, a Swedish study showed that total costs per patient over 16 weeks of treatment were reduced by 11% when a combined epoetin beta/iron sucrose protocol was used as compared with epoetin beta alone.

Although the pharmacoeconomic studies looking at cost-effectiveness were performed in Switzerland, similar savings may be possible in other countries (Latin America) due to the decrease in costs to the health-care system associated with fewer infusions and a sensible reduction in ESAs annual cost. Therefore, in the specific case of patients with anaemia and CKD, ferric Carboxymaltose may provide additional economic advantages.

## **OBJECTIVE**

### *Primary:*

- To determine possible reduction in ESA requirements after intravenous 1g Ferric Carboxymaltose (FERINJECT ®) administration in patients with CKD in pre-dialysis stage, who were under a monthly EPO treatment and continuous oral iron therapy during the previous six months, in order to maintain a Hb value according to international recommendations.

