### *Secondary:*

- To assess the number of hospitalizations pre (six months) and post (six months) intravenous 1g Ferric Carboxymaltose (FERINJECT ®) administration in patients with CKD in pre-dialysis stage.
- To record the need for transfusion pre (six months) and post (six months) intravenous 1g Ferric Carboxymaltose (FERINJECT ®) administration in patients with CKD in pre-dialysis stage.
- To evaluate renal function as measured by Creatinine clearance and proteinuria of 24 hours, pre (six months) and post (six months) intravenous 1g Ferric Carboxymaltose (FERINJECT ®) administration in patients with CKD in pre-dialysis stage.
- To analyze the number of adverse reactions and complications due to intravenous 1g Ferric Carboxymaltose (FERINJECT ®) administration in patients with CKD in pre-dialysis stage.

[figure not shown]

[name]; PhD; FASN.  
Professor of Medicine University of Buenos Aires  
Chief of Nephrology.  
Hospital Alemán, [name]  
Buenos Aires (1118)- Argentina  
[contact]  
[contact]  
Mobile [contact]  
E-mail: [contact]

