## **STUDY DESIGN**

- Prospective study to 6 months with a single branch of patients who are treated with monthly EPO therapy together with oral iron for at least the last six months before the study and met inclusion criteria.
- From CKD database are randomly selected 30 patients. After signing an informed consent form in duplicate and with witness, duly authorized by the Committee on Education and Research institutions, all patients will receive intravenous 1g Ferric Carboxymaltose (FERINJECT ®) in one dose of 1000 mg on the recommendation of the product.
- On a monthly basis after intravenous 1g Ferric Carboxymaltose (FERINJECT ®) the administration, all patients will be controlled dosage of Hb by HemoCue, in order to dispense the EPO to maintain a baseline Hb level.
- Monthly checks will be carried to register: vital signs and weight control, and record of adverse reactions linked to 1g Ferric Carboxymaltose (FERINJECT ®) administration, registration HemoCue results.
- Before FERINJECT treatment and then every two months, all patients underwent blood control that includes: complete blood count haematimetric indexes, platelet count, serum iron, serum ferritin, TSAT, CRP, urea, creatinine, liver function tests).
- There will be collection of 24-hour urine to measure Creatinine Clearance and proteinuria at baseline and at the end of the study.

[figure not shown]

[name]; PhD; FASN.  
Professor of Medicine University of Buenos Aires  
Chief of Nephrology.  
Hospital Alemán, [name]  
Buenos Aires (1118)- Argentina  
[contact]  
[contact]  
Mobile [contact]  
E-mail: [contact]

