## **METHODS**

This is a pilot, open label study in which the population will be formed by adult patients either gender, with CKD in pre-dialysis stage in Buenos Aires, Argentina, that fulfill the inclusion and exclusion criteria previously established.

Once signed the informed consent, the patients will be included in the study an initial check-up will be performed in order to evaluate clinical status and to assess haematology parameters in every patient.

After that the patients will receive intravenous Ferric Carboxymaltose (Ferinject ®) by the following therapeutic schedule:

Visit 2: IV FERINJECT ® 1000 mg in an infusion over 15-20 minutes.

Then, a monthly evaluation will be performed by six months.

During the time of the investigation there will be strict control of adverse effects in every patient and that will be recorded in the corresponding CRF.

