### Visit 2:

- a) Anamnesis and Physical Examination (Vital signs: blood pressure, heart rate, breath rate, etc).
- b) IV Ferinject ® 1000 mg administration.
- c) Evaluation of tolerability and adverse effects.

### Visit 3

- a) Anamnesis and Physical Examination (Vital signs: blood pressure, heart rate, breath rate, etc).
- b) Evaluation of tolerability and adverse effects.
- c) Blood samples for Hb, Htc. RBC, serum ferritin, transferrin saturation, creatinine clearance and proteinuria.

### Visit 4 to 8

- a) Anamnesis and Physical Examination (Vital signs: blood pressure, heart rate, breath rate, etc).
- b) Evaluation of tolerability and adverse effects.
- c) Blood samples for Hb, Htc. RBC, serum ferritin, transferrin saturation, creatinine clearance and proteinuria.
- d) Adjustment of medication according to the Hb and TSAT outcomes.

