### Potential results post FERINJECT ®

### Measure to follow

|                                  |                                  |
|----------------------------------|----------------------------------|
| 1- Hb 12-13 (g/dl) TSAT (%) > 20 | NO Ferinject NO Epo              |
| 2- Hb 12-13 (g/dl) TSAT (%) < 20 | Ferinject 100mg NO Epo           |
| 3- Hb 11-12 (g/dl) TSAT (%) > 20 | NO Ferinject increase Epo 25%    |
| 4- Hb 11-12 (g/dl) TSAT (%) < 20 | Ferinject 200mg NO Epo           |
| 5- Hb 10-11 (g/dl) TSAT (%) > 20 | NO Ferinject increase Epo 25%    |
| 6- Hb 10-11 (g/dl) TSAT (%) < 20 | Ferinject 300mg increase Epo 25% |

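### The objectives name a single 1 g dose of ferric carboxymaltose as the exposure, but the dosing table for visits 4 to 8 orders more iron whenever TSAT is below 20 and Hb is 10 to 13 g/dl

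*Protocol*

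**What the plan says.** **Objectives.** The primary objective is "To determine possible reduction in ESA requirements after intravenous 1g Ferric Carboxymaltose" in pre-dialysis CKD patients already on monthly EPO and oral iron. All four secondary objectives name the same gram. The first reads "To assess the number of hospitalizations pre (six months) and post (six months) intravenous 1g Ferric Carboxymaltose". The fourth goes further and attributes adverse reactions and complications causally to the 1 g administration.

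**Design and methods.** STUDY DESIGN gives the treatment "in one dose of 1000 mg on the recommendation of the product". The therapeutic schedule in METHODS has one entry: "Visit 2: IV FERINJECT ® 1000 mg in an infusion over 15-20 minutes". Neither section mentions later iron.

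**Visit schedule.** Under Chronogram of visits, Visit 4 to 8, item d is "Adjustment of medication according to the Hb and TSAT outcomes". The six-row table headed Measure to follow comes directly after it. Rows with TSAT above 20 give no iron, for example "1- Hb 12-13 (g/dl) TSAT (%) > 20 | NO Ferinject NO Epo". Rows with TSAT below 20 all give iron, for example "4- Hb 11-12 (g/dl) TSAT (%) < 20 | Ferinject 200mg NO Epo".

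**Variables.** The dependent variables include the amount of erythropoietin. The independent variables list only cardiovascular drugs. Cumulative iron dose appears in neither list.

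**The concern.** The objectives and the dosing rule describe two different treatments: a single gram, and a gram followed by top-ups guided by TSAT. A report written to the objectives would present the ESA change as what follows 1 g, although some patients may have received more iron before the six-month assessment. The same applies to safety: a reaction to a later infusion would be counted among those caused by the gram.

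The study has one arm, so no comparator can separate the effect of the first gram from that of the later doses. What is at stake is the meaning of the primary and safety results, in particular whether a reader may conclude that one 1 g infusion is enough to produce them.

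**Working it through.** The protocol gives no effect size, standard deviation or power that bears on this point. The check is a side-by-side reading and simple dose arithmetic.

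**1. What the table orders (Measure to follow)**

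| Hb (g/dl) | TSAT > 20 | TSAT < 20 |
|---|---|---|
| 12-13 | no iron; NO Epo (row 1) | 100 mg; NO Epo (row 2) |
| 11-12 | no iron; EPO +25% (row 3) | 200 mg; NO Epo (row 4) |
| 10-11 | no iron; EPO +25% (row 5) | 300 mg; EPO +25% (row 6) |

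Three of the six rows order iron, and together they cover Hb 10 to 13 g/dl. Total iron stays at the named 1000 mg only for a patient who never falls in a TSAT < 20 row.

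**2. One re-dose.** Total = 1000 mg + table dose.

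- Row 2: 1000 + 100 = 1100 mg; 100/1000 = +10%
- Row 4: 1000 + 200 = 1200 mg; 200/1000 = +20%
- Row 6: 1000 + 300 = 1300 mg; 300/1000 = +30%

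**3. Repeated re-dosing.** Total = 1000 mg + k × table dose, where k is the number of re-dosing visits. The protocol gives two TSAT schedules. The visit list has TSAT at every visit from 3 to 8, so k is at most 5 (visits 4 to 8). STUDY DESIGN has it every two months, for which I assume k = 2 to 3 within visits 4 to 8.

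| Same row each time | k = 2 to 3 | k = 5 (ceiling) |
|---|---|---|
| Row 2 | 1200-1300 mg | 1500 mg (+50%) |
| Row 4 | 1400-1600 mg | 2000 mg (+100%) |
| Row 6 | 1600-1900 mg | 2500 mg (+150%) |

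**4. What the ceilings do and do not measure.** They describe iron exposure only. Reaching 2500 mg requires row 6 at all five visits, and row 6 also raises EPO by 25% each time. If those increases compound, 1.25^5 = 3.05 times the starting EPO. That patient shows a large rise in ESA use, not a spurious fall.

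**5. Effect on EPO.** This would need the number of patients re-dosed, when, and in which row. The protocol gives none of these, so no figure can be derived.

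**The case against.** **The gram is only a time anchor.** The primary objective looks at what happens after the gram, and three secondary objectives compare six months before with six months after it. On this view the gram is the index event, and the re-dosing is disclosed openly in the same protocol. This is a fair reading of those four objectives taken alone. It does not survive the safety objective, which attributes reactions causally to the 1 g administration, or STUDY DESIGN, which fixes the treatment as a single dose.

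**A 30-patient, single-arm, open-label pilot could not credit a change to exactly 1 g anyway.** True, but that is no reason to name the wrong exposure.

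**Late doses hardly matter.** The protocol does not date the visits. If Visit 3 is month 1, Visit 8 is month 6, and iron given then could barely affect six-month EPO. This stands, and is a further reason not to lean on the ceilings.

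**Counts and descriptive analyses belong in the SAP.** They may well sit there. The objectives and the dosing rule are protocol content, however, and the conflict lies between them.

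**Stronger readings to avoid.** A reader might infer from rows 3 and 4 that a patient whose TSAT did not respond to the gram is recorded as an ESA reduction. At Hb 11-12, row 3 is "3- Hb 11-12 (g/dl) TSAT (%) > 20 | NO Ferinject increase Epo 25" per cent, while row 4 gives iron and NO Epo. That inference needs NO Epo to mean withheld; if it means no increase, EPO is unchanged and no reduction is recorded. The protocol does not settle which is meant. It is also a separate problem of the table's EPO rule, limited to one of three Hb bands, and rewording the objectives would not cure it. Nor does the absence of iron dose from the variable lists show that doses go unrecorded, because the data forms (Appendix 1) are not available to read.

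**Conclusion.** The inconsistency is real. The objectives, design and methods define the exposure as one 1 g dose, while the algorithm for visits 4 to 8 adds 100, 200 or 300 mg when TSAT is below 20 and Hb is 10 to 13 g/dl. In re-dosed patients, the ESA change and the adverse reactions credited to 1 g reflect 1 g plus TSAT-guided re-dosing. One re-dose exceeds the named dose by 10%, 20% or 30%.

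This rests on taking the table as the rule for item d at visits 4 to 8, which its position supports. The amount by which the EPO result is affected cannot be stated. It is nil for a patient never re-dosed, and nil overall if nobody is. Re-dosing itself may be clinically sensible; the fault is that the objectives do not name it. The point should be corrected because it changes what the trial may conclude, but wording and reporting are enough to do so.

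**What to change.** - Restate the primary and secondary objectives with the exposure as *1 g followed by TSAT-guided re-dosing*, and refer to the table in STUDY DESIGN and METHODS.
- Add cumulative iron dose and number of infusions under Independent variables, since they are exposures rather than outcomes.
- Report how many patients were re-dosed. This count tells a reader whether the matter is trivial or material.
- Attribute each adverse reaction to the infusion it follows.
- Show EPO change up to the first re-dose as a descriptive analysis only. That follow-up ends because TSAT is low, so the patients who remain are selected on response.

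No change to dose, visits or sample size is needed. The cost is a narrower claim and slightly more reporting. The different EPO action in rows 3 and 4 at Hb 11-12 needs its own clarification, starting with what NO Epo means.

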### *Secondary:*

- To assess the number of hospitalizations pre (six months) and post (six months) intravenous 1g Ferric Carboxymaltose (FERINJECT ®) administration in patients with CKD in pre-dialysis stage.
- To record the need for transfusion pre (six months) and post (six months) intravenous 1g Ferric Carboxymaltose (FERINJECT ®) administration in patients with CKD in pre-dialysis stage.
- To evaluate renal function as measured by Creatinine clearance and proteinuria of 24 hours, pre (six months) and post (six months) intravenous 1g Ferric Carboxymaltose (FERINJECT ®) administration in patients with CKD in pre-dialysis stage.
- To analyze the number of adverse reactions and complications due to intravenous 1g Ferric Carboxymaltose (FERINJECT ®) administration in patients with CKD in pre-dialysis stage.

[figure not shown]

[name]; PhD; FASN.  
Professor of Medicine University of Buenos Aires  
Chief of Nephrology.  
Hospital Alemán, [name]  
Buenos Aires (1118)- Argentina  
[contact]  
[contact]  
Mobile [contact]  
E-mail: [contact]

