### **Inclusion Criteria**

- Patients over 18 years with chronic kidney disease (Creatinine Clearance  $\leq$  40 ml / min), and Hb between 11-12 g / dl, serum ferritin <100 mg / dl, or TSAT <20, being treated with a regular (monthly) institution schedule for EPO together with oral iron during the last 6 months before inclusion.

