### **Patient withdrawal**

All patients of the population study may withdraw any time from the investigation by own will or by the investigator's decision before the occurrence of any adverse effect or transitory disease that could alter the results of the study or that represents a contraindication for the administration of the medicine. The reasons for withdrawal will have to be documented.

[figure not shown]

[name]; PhD; FASN.  
 Professor of Medicine University of Buenos Aires  
 Chief of Nephrology.  
 Hospital Alemán, [name]  
 Buenos Aires (1118)- Argentina  
 [contact]  
 [contact]  
 Mobile [contact]  
 E-mail: [contact]

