## **VARIABLES**

### *1-Dependent Variables*

- Heart rate
- Breath rate
- Blood pressure
- Severity of the Anemia: According to the classification established by the WHO.
- Hemoglobin: substance inside erythrocytes consisting of a protein that binds iron
- Hematocrit: Proportion of erythrocytes in plasma
- Mean Corpuscular Volume (MCV): cellular index that reflects erythropoiesis.
- Serum Ferritin
- Percentage of transferrin saturation
- Creatinine Clearance
- Proteinuria
- Amount of Erythropoietin.
- Number of transfusions
- Number of hospitalizations
- Death
- Cause of Death
- Adverse Events: Appearance of adverse reactions in the organism with the treatment administered. Among others: nausea, vomiting, headache, diarrhea, allergy and hypotension.

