## **STATISTICS**

All statistical analyses will be processed through GraphPad Prism version 4.0 (GraphPad Software, Inc. San Diego, CA). Initially, a descriptive statistic of the sociodemographic, clinical and laboratory characteristics will be performed of all the participant patients of the study, directed to describe patient population. Then, calculation of absolute frequencies, proportions, measures of central tendency and dispersion of the involved variables will be performed. When evaluating parameters with a Gaussian distribution, comparisons will be carried out using t-test. For those parameters with a non-Gaussian distribution, comparisons will be performed by non-parametric methods using the Wilcoxon rank sum test. Values will be expressed as mean  $\pm$  SD, and  $p < 0.05$  will be considered significant.

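### Hospitalizations and transfusions are compared as raw six-month counts with no allowance for a post-infusion window cut short by withdrawal or death

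*Protocol*

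**What the plan says.** The protocol's secondary objectives set equal nominal windows before and after the infusion: "To assess the number of hospitalizations pre (six months) and post (six months) intravenous 1g Ferric Carboxymaltose" and "To record the need for transfusion pre (six months) and post (six months) intravenous 1g Ferric Carboxymaltose". The list of dependent variables defines the first as "Number of hospitalizations" and gives transfusions likewise as a number. It also lists death and its cause. For the primary objective the list has only "Amount of Erythropoietin", with no unit of time.

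The inclusion criteria require patients "being treated with a regular (monthly) institution schedule for EPO together with oral iron during the last 6 months before inclusion". Follow-up after infusion is monthly for six months. The withdrawal section says "All patients of the population study may withdraw any time from the investigation by own will or by the investigator's decision". It ties withdrawal to adverse effects or intercurrent illness that might affect the results, and asks that reasons be documented.

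The Statistics section gives one general rule, "When evaluating parameters with a Gaussian distribution, comparisons will be carried out using t-test", with the Wilcoxon rank sum test for non-Gaussian variables. No section mentions time observed, a rate or an exposure adjustment.

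**The concern.** A count can be compared between two periods only if both were observed for the same length of time. Here every patient has six months at risk before inclusion, because eligibility demands it. Nothing guarantees the six months afterwards. A patient who withdraws or dies at month 3 has had half the time in which to be admitted or transfused. A raw count does not register this, so the shortfall reads as fewer events.

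The shortfall is larger if those who leave are the sicker patients with more events. The study has one arm, so no control group with the same attrition would expose the artefact. At stake is whether a lower post-infusion count can be read as fewer admissions or transfusions at all.

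**Working it through.** The protocol gives a sample of 30 but no event rate, effect size, drop-out rate or power, so there is no stated figure to reproduce.

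**Is the planned window itself short?** The timelines put the last patient's first visit at 09/11/2012 and last visit at 10/05/2013, which is 182 days. The planned window is about six months, so only early leaving shortens it.

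**Inputs.** From the protocol: n = 30, two six-month windows, a full pre window by eligibility. Assumed: the share leaving *d* (or number leaving *k*), the mean month of exit *m*, and the ratio *r* of leavers' event rate to that of the others. Assumed throughout: no treatment effect, each patient's event rate constant over both windows, and leavers' partial counts kept.

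**1. Equal event rates.** Apparent reduction = d × (1 − m/6).

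| Share leaving | Exit at month 1 | Month 3 | Month 5 |
|---|---|---|---|
| 10% (3 of 30) | 8.3% | 5% | 1.7% |
| 20% (6 of 30) | 16.7% | 10% | 3.3% |
| 30% (9 of 30) | 25% | 15% | 5% |

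**2. Leavers with a higher rate, exit at mid-window.** Post/pre count = [(30 − k) + 0.5kr] / [(30 − k) + kr].

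- k = 3, r = 1: 28.5/30 = 0.950. r = 3: 31.5/36 = 0.875.
- k = 6, r = 1: 27/30 = 0.900. r = 3: 33/42 = 0.786.

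**3. Effect on the test.** Simulation used n = 30, exit uniform over the window, and an assumed mean of 0.3 or 1.0 hospitalizations per six months with gamma heterogeneity. A paired t-test gave a false significant reduction in about 3% of runs at 10% leaving, 4–6% at 20% and 4–8% at 30%. The nominal figure is 2.5% per side. The main harm is therefore to the estimate, and inflation of the test is modest.

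**4. Does a rate cure it?** With equal event rates, dividing by time observed returns a null reduction of 0% for every *d*. With unequal rates the comparison must also be within patient. Take k = 3, r = 3, with one event per six months in stayers:

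- Pooled pre rate: 36 events / 180 patient-months = 0.200.
- Pooled post rate: 31.5 / (27 × 6 + 3 × 3 = 171) = 0.184.
- Ratio: 0.921, still biased, because leavers contribute less post time.

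Conditioning on patient removes this. A leaver's expected total is 3 + 1.5 = 4.5 events, and the post share of time is 3/(6 + 3) = 1/3, so 1.5 post events are expected, as occurs. The rate ratio is then 1.

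**5. EPO.** If the amount were read as a six-month total, a mid-window leaver on an unchanged dose would show a false 50% reduction. With an assumed between-patient log-SD of 0.5 and within-patient log-SD of 0.1–0.3, a paired t-test gave false reductions in 7–12% of runs at 10% leaving and 17–37% at 20%. An unpaired rank sum test gave at most 0.6% and 1–3%. Per month observed, the paired t-test stayed near nominal (about 2.0–2.7% across 10–30% leaving). These figures apply only under the total-dose reading.

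**The case against.** **The harm needs a rule that the protocol does not contain.** The bias arises only if partial counts are kept. The protocol does not say how leavers enter the comparison, and that is commonly left to the SAP, which is not at hand. A completers-only comparison shows none of this bias. This stands, so the bias is conditional. It does not remove the point: the choice of a count over a rate is made in the protocol, and a completers-only analysis swaps truncation for selection, possibly of the patients with most events.

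**The primary outcome.** A reader might infer that the EPO comparison is biased too. The text does not support that. The amount has no time unit, the primary objective speaks of ESA requirements under monthly treatment, and EPO is dispensed against a monthly Hb. A monthly dose fits as well as a total.

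**Direction.** A reader might also infer that every error favours Ferinject. Truncation does, but the pre window is complete only in time at risk. The data collection section relies on direct patient evaluation and names no source for pre-window admissions or transfusions. Under-recording there would push the other way.

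**Attrition may be low.** Expected haemodialysis within six months, decompensated heart failure and life expectancy under a year are all excluded. This limits early leaving but does not abolish it. No section makes dialysis start the end of follow-up, so withdrawal and death are the documented routes.

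**Conclusion.** The point holds for hospitalizations and transfusions, conditionally. They are defined as raw numbers over windows of which only the first is guaranteed complete, with no denominator. If partial counts are kept, the comparison leans towards a reduction: about 5% with 10% leaving at mid-window and 10% with 20% leaving. If leavers have three times the event rate, the figures are 12.5% and about 21%. Drop-out share, exit time and rate ratio are all assumptions. If nobody leaves, the bias is nil.

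For EPO the supportable conclusion is narrower: the unit of the primary measure is not stated, and one possible reading would carry the same bias. The net direction of error across all sources is not established, because recording in the pre window is undocumented. The matter is worth correcting because the change is cheap and the design cannot detect the artefact, but it does not by itself invalidate a 30-patient pilot.

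**What to change.** In the secondary objectives, the list of dependent variables and the Statistics section:

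- Define hospitalizations and transfusions as events per patient-month observed. Post time runs from infusion to last contact, withdrawal, death or the end of six months; pre time is the six months before infusion.
- Compare within patient, for example by Poisson regression conditional on patient with log(days observed) as offset. Keep every infused patient in the reported rates, and state that patients with no events in either window do not inform the conditional model.
- Record the exit date. The protocol asks for the reason for withdrawal and for death and its cause, but names no date. Report total observed days in each window.
- State the EPO measure as mean units per month observed in each window.
- State in advance how withdrawal, death and any start of dialysis enter the comparison. Add a sensitivity analysis for illness-related withdrawal or death: where worsening illness both changes the event rate and triggers exit, a rate does not correct the bias.

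The cost is wording, one date field and slightly more analysis; visits and treatment are untouched. Rates from very short follow-up will be imprecise, and the apparent reduction may be smaller.
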